**Dropouts**

Participants choosing to discontinue the study for any reason will be followed according to the intention to treat principle. All drop-outs will be registered, as well as their reason for discontinuing participation, if the participant chooses to supply this information.

Participants who take supplements of selenium or Q10 for any reason outside the study will be regarded as dropouts.

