**Inclusion criteria**

Individuals living in the municipality of Kinda, aged between 70-80 years who have accepted participation in the study, and who are expected to fulfill a study period of 4 years.

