**Exclusion criteria**

Recent myocardial infarction (within 4 weeks).

Planned cardio-vascular operative procedure within 4 weeks.

Hesitation concerning if the candidate can decide for him/herself whether to participate in the study or not, or if he/she understands the consequences of participation.

Serious disease that substantially reduces survival or where it is not expected that the participant can cooperate for the full 4 year period.

Other factors making participation unreasonable, such as long/complicated transport to the Primary Health Center where the project is managed, or drug/alcohol abuse.

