**Concomitant pharmacological treatment**

Participants who have been prescribed pharmacological drugs due to concomitant diseases/medical conditions are advised to continue treatment.

Participants who have been prescribed anticoagulants containing warfarin are advised to continue treatment, but it is recommended that they analyze the INR at the start of the intervention with selenium and Q10, and again after 2 weeks. Interactions between selenium/Q10 and warfarin have been discussed in literature but have not been demonstrated.

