**Permission from the Swedish Medical Products Agency**

Contact has been taken with the Medical Products Agency in Sweden regarding permission to use the preparations during the intervention. However, the principal investigator of the project has been orally informed by the Agency that since this was not regarded as a trial of a medication, but rather of food supplement commodities that are readily available as commercial goods, the Agency would not review the study protocol.

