**Basic power calculation**

Using the assumption that the incidence of occurrences in the placebo group during a follow up of 4 years is 40%, and 28% in the intervention group, i.e. a difference in incidence between the groups of 30% and an absolute difference of 12%, 244 individuals are needed in order to obtain a statistical power of 80% with a significance level of 5%. A dropout frequency of 15% is to be expected, which is why a minimum of 560 individuals is needed in order to obtain significant differences.

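### Outside use of selenium or Q10 makes a participant a dropout, yet no listed eligibility criterion screens for current use before randomisation

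*Protocol*

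**What the plan says.** Five sections of the protocol bear on this.

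- **Dropouts**, on outside use: "Participants who take supplements of selenium or Q10 for any reason outside the study will be regarded as dropouts". The rule sets no limit on dose, duration or timing.
- **Dropouts**, on leaving: "Participants choosing to discontinue the study for any reason will be followed according to the intention to treat principle". The section also has all dropouts registered, with the reason where the participant gives one.
- **Inclusion criteria**: "Individuals living in the municipality of Kinda, aged between 70-80 years who have accepted participation in the study", plus an expectation of completing four years. Supplement use is not mentioned.
- **Exclusion criteria**: none of the listed items names selenium or Q10. The nearest is an open-ended one: "Other factors making participation unreasonable, such as long/complicated transport to the Primary Health Center where the project is managed, or drug/alcohol abuse". The section on concomitant treatment deals with prescribed drugs and does not mention supplements bought by the participant.
- **Permission from the Swedish Medical Products Agency**: the products are "food supplement commodities that are readily available as commercial goods".

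**The concern.** The plan treats outside use as incompatible with being a full participant, but has no stated step that finds it before randomisation. Someone already taking either supplement meets the listed criteria, is allocated, and falls under the dropout rule at once if the habit continues. That could have been settled at screening, where it costs nothing in validity.

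After randomisation there are two ways to handle such a person, and each has a price.

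- **Kept in the analysis.** A placebo-arm user may receive active substance, and the difference between the arms shrinks.
- **Removed.** Who is compared then depends on behaviour after allocation, which may be related to prognosis, so randomisation no longer protects the comparison.

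These are alternatives. The same person cannot cause both.

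**Working it through.** **Inputs.** From the Basic power calculation: 40% events on placebo and 28% on active over 4 years, 80% power, 5% significance, 244 individuals, 15% dropout, at least 560 in total. Assumed: 1:1 allocation and a two-sided test, since neither is stated. The rate of outside use, c, is not in the documents; 5 to 20% is assumed.

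**Step 1: reproduce the plan's figure.** With p1 = 0.40, p2 = 0.28 and mean p = 0.34,

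n per arm = [1.960 × √(2p(1−p)) + 0.8416 × √(p1(1−p1) + p2(1−p2))]² / (p1−p2)²

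= [1.960 × 0.6699 + 0.8416 × 0.6645]² / 0.12² = 1.8723² / 0.0144 = 243.4, so 244.

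The stated 244 is therefore a per-arm number, 488 in total. Dropout inflation gives 488/0.85 = 574.1 (575), or 488 × 1.15 = 561.2 (562). The stated 560 is close to both and means 280 per arm.

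**Step 2: outside users kept in the analysis.** Suppose a share c of the placebo arm gets the full active-arm benefit and the active rate stays at 28%. The placebo rate becomes 0.40 − 0.12c. Then

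power = Φ[(d − 1.960 × se0) / se1],

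where d is the difference in rates, se0 = √(2p(1−p)/n) and se1 = √((p1(1−p1) + p2(1−p2))/n).

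For c = 0 and n = 280: (0.12 − 1.960 × 0.04004)/0.03971 = 1.046, power 85.2%.

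For c = 10% and n = 280: (0.108 − 1.960 × 0.03986)/0.03960 = 0.754, power 77.47%.

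| c (assumed) | Placebo rate | Difference (points) | Power, 280 per arm | Power, 244 per arm |
|---|---|---|---|---|
| 0 | 40.0% | 12.0 | 85% | 80.1% |
| 5% | 39.4% | 11.4 | 82% | 76.1% |
| 10% | 38.8% | 10.8 | 77% | 71.7% |
| 15% | 38.2% | 10.2 | 73% | 66.9% |
| 20% | 37.6% | 9.6 | 68% | 61.8% |

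The 280 column supposes that all 560 are analysed. In it, power crosses 80% somewhere between 5 and 10% use.

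**Step 3: outside users removed.** If 15% are removed, 280 × 0.85 = 238 per arm remain and power is 79.1%. The allowance thus roughly covers 15% lost numbers from all causes together. It does not cover dilution, and it cannot repair selective removal, whose direction cannot be calculated from the documents.

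**Step 4: is removal stated?** The two Dropouts sentences differ in scope. One follows people who choose to stop. The other classifies people by what they take, whether or not they want to stop. Nothing says that the second group leaves follow-up or analysis, and nothing says outright that the first sentence covers them. The 15% inflation treats dropouts as lost numbers, which leaves the removal reading open without establishing it.

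**The case against.** The strongest reply has four parts.

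- **Removal is not the plan.** A reader might infer that the protocol takes willing participants out of the trial. The text does not support that. The natural reading of the Dropouts section is that outside users join a class that is registered and followed by intention to treat. Assignment to analysis sets is also commonly left to the SAP. This stands, so the second part of the fix is only a clarification.
- **The placebo arm is not shown to be contaminated.** Commercial availability is not evidence of use in this population, and no rate is given. This stands: contamination is a risk of unknown size.
- **The power losses are a worst case.** The rule covers either supplement at any dose for any time, while the trial tests both together for 48 months. Use of one product, or low-dose or brief use, would dilute less. At 5% use power is still 82% if all 560 are analysed. This stands, and the table must be read as an upper bound for each assumed rate.
- **The open-ended exclusion item could be used to refuse current users.** It could, but its examples are transport and substance abuse, and it does not prompt staff to ask about supplements. The gap remains.

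It may also be said that excluding users is a design preference that costs recruits. The Participants section plans 500-600 people and the power calculation needs 560. If 600 were available and 10 to 20% were users, 600 × 0.90 = 540 or 600 × 0.80 = 480 would remain. That cost is real if use is common. Most of it is already built into the present rule, however, which counts the same people as dropouts if they continue.

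**Conclusion.** The point holds as a gap at entry. The protocol's own rule makes outside users dropouts, it calls the products readily available, and no listed criterion screens for current use, so a continuing user can be a dropout from the day of randomisation. Eligibility belongs in the protocol and cannot wait for the SAP.

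The size is unknown. As an upper bound, power at 280 per arm falls from 85% to 82, 77, 73 and 68% at 5, 10, 15 and 20% use. This assumes 1:1 allocation, a two-sided test, all 560 analysed, full benefit in every placebo-arm user and an unchanged active-arm rate.

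Two stronger conclusions should not be drawn: that outside users are to be removed, and that dilution and selective removal add up. The first is not stated, and the second is impossible for the same person. Any protocol text after the Basic power calculation was not available to check.

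**What to change.** (a) Add current use of selenium or Q10 supplements to the Exclusion criteria, asked of every candidate before randomisation. This costs one screening question and a somewhat smaller eligible pool. Recruitment should be checked against the 560 minimum, bearing in mind that those excluded would otherwise be dropouts under the present rule if they continued.

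(b) As a clarification, replace the outside-use sentence under Dropouts with wording to this effect: participants who start taking selenium or Q10 outside the study stay in follow-up and are analysed in their randomised arm, and the use is recorded as a protocol deviation for a sensitivity analysis. This costs only wording and a line in the visit record.

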**Ethical permission**

Ethical permission shall be accepted from the Ethical Review Board before the start of the study. Oral and written “patient” information will be given to all participants, as well as a signed copy of the consent form .

**Permission from the Swedish Medical Products Agency**

Contact has been taken with the Medical Products Agency in Sweden regarding permission to use the preparations during the intervention. However, the principal investigator of the project has been orally informed by the Agency that since this was not regarded as a trial of a medication, but rather of food supplement commodities that are readily available as commercial goods, the Agency would not review the study protocol.

**Participants**

500-600 healthy individuals as well as patients treated for various diseases and already participating in the former epidemiological heart failure study in the Kinda municipality.

**Basic power calculation**

Using the assumption that the incidence of occurrences in the placebo group during a follow up of 4 years is 40%, and 28% in the intervention group, i.e. a difference in incidence between the groups of 30% and an absolute difference of 12%, 244 individuals are needed in order to obtain a statistical power of 80% with a significance level of 5%. A dropout frequency of 15% is to be expected, which is why a minimum of 560 individuals is needed in order to obtain significant differences.

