**Randomizing**

The randomising procedure will be performed using PharmaNord’s computer assisted randomization in blocks of 6.

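### The sample-size paragraph presents a per-group number (244) as the number of individuals needed, its minimum of 560 falls slightly short after 15% loss, and the planned range of 500-600 starts below that minimum

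*Protocol*

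**What the plan says.** The Basic power calculation section assumes that "the incidence of occurrences in the placebo group during a follow up of 4 years is 40" per cent, against "28% in the intervention group". It describes this as "a difference in incidence between the groups of 30% and an absolute difference of 12" percentage points. From these inputs it concludes that "244 individuals are needed in order to obtain a statistical power of 80% with a significance level of 5" per cent. It does not say whether 244 is per group or in total, and it does not say whether the test is one- or two-sided.

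It then allows for 15% dropout, "which is why a minimum of 560 individuals is needed in order to obtain significant differences". No inflation formula is shown.

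The Participants section gives the planned size as "500-600 healthy individuals as well as patients treated for various diseases". The Randomizing section specifies "computer assisted randomization in blocks of 6" and gives no allocation ratio. The Dropouts section says that people who discontinue will still be followed, under intention to treat.

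**The concern.** A 15% allowance cannot take a total of 244 to 560, which is an increase of 130% (560/244 = 2.30). So the paragraph does not follow from its own numbers until the reader supplies the missing words. Separately, a trial that closed recruitment at 500 would satisfy the Participants section and miss the minimum in the Basic power calculation.

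This paragraph is the protocol's justification of its size. A reader should be able to take from it how many people are to be randomised, how many are needed with outcome data, and what power follows. At present the first answer depends on the section consulted, the second is mislabelled, and the third depends on an unstated view of what happens to dropouts.

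**Working it through.** **Inputs.** From Basic power calculation: p1 = 0.40, p2 = 0.28, difference 0.12, power 80%, significance level 5%, dropout 15%. From Participants: 500-600. Assumed: two-sided test and 1:1 allocation to two arms, which blocks of 6 allow.

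**Step 1: reproduce 244.** Pooled two-proportion formula, mean rate 0.34:

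n per group = [1.96 × √(2 × 0.34 × 0.66) + 0.8416 × √(0.40 × 0.60 + 0.28 × 0.72)]² / 0.12²

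= [1.96 × √0.4488 + 0.8416 × √0.4416]² / 0.0144 = 243.4, so **244 per group, 488 in total**.

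Other common choices give, per group: unpooled 241, arcsine 243, continuity-corrected 260, one-sided 192, one-sided with continuity correction 208. None makes 244 a total; the smallest still needs 2 × 192 = 384. The exact match supports the two assumptions.

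**Step 2: power if 244 were the total.** With n per group,

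power = Φ{[0.12 × √n − 1.96 × √0.4488] / √0.4416}.

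At n = 122 this is 50.7%. At n = 244 it is 80.1%.

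**Step 3: where 560 comes from.** 244 × 1.15 = 280.6; cut to 280 and doubled, this is 560 (488 × 1.15 = 561.2). So 560 fits a doubled 244 multiplied by 1.15. That route is inferred, because the protocol shows none.

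**Step 4: does 560 deliver 488 after 15% loss?** 560 × 0.85 = 476, which is 12 short of 488; power is 79.1%. To keep 488 after losing 15%: 488 / 0.85 = 574.1, so 575 in total, or 576 as 288 per group.

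**Step 5: power across the planned range.** Same formula, under two readings of dropout:

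| Randomised | Left after 15% loss of outcome | Power | Power with complete follow-up at the assumed rates |
|---|---|---|---|
| 500 | 425 | 74.4% | 81.0% |
| 560 | 476 | 79.1% | 85.2% |
| 576 | 489.6 | 80.2% | not computed |
| 600 | 510 | 81.8% | 87.5% |

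**Step 6: a third reading, for illustration only.** Suppose that dropouts are followed, but that the 15% in the active arm have the placebo rate. The active-arm rate becomes 0.85 × 0.28 + 0.15 × 0.40 = 0.298 and the difference 0.102. With 250 per group, power is about 67%. The protocol does not make this assumption; it shows only that complete follow-up does not by itself secure 81%.

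**The case against.** The strongest reply is that the paragraph corrects itself. The 560 in the next sentence makes sense only if 244 is per group, so adding the missing words changes no enrolment figure. That stands. A reader might infer from the literal text that the trial was planned with 51% power; the documents do not support this.

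A reader might also infer that the authors used a wrong dropout formula. Multiplying by 1.15 fits, but no formula is stated, and the effect is about one percentage point of power. What does not depend on the inference is that 560 less 15% falls 12 short of 488.

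A third reply is that 74% at 500 assumes that all dropouts lose their outcome, whereas the Dropouts section intends to follow them. This also stands: the flat statement that the lower end of the range lacks 80% power is not established, since complete follow-up at the assumed rates gives 81.0%. But the Basic power calculation itself treats dropout as a loss and sets 560 for that reason. If follow-up is expected to be complete, the 560 minimum is unnecessary; if not, 500 is too few. The two sections need reconciling either way.

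Finally, the Participants section is a short description with no rule for ending recruitment, and 560 lies within its range. That softens the mismatch without removing it. The remark about obtaining significant differences could be read as promising a result, but the sentence before it speaks correctly of power, so this is loose wording.

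**Conclusion.** The point holds, at moderate severity.

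- The figure of 244 individuals for 80% power is wrong as written. It is the number per group, and 488 are needed in total. This is a labelling error and did not set the planned size.
- The minimum of 560 gives 79.1% rather than 80% if 15% are lost to outcome, a minor shortfall.
- The range of 500-600 starts 60 below the protocol's own minimum. This comparison needs no statistical assumption. Its consequence does: at 500, power is about 74% with 15% loss of outcome data and 81% with complete follow-up at the assumed rates.

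The power figures rest on a two-sided 5% test, 1:1 allocation, the pooled normal approximation and the stated rates of 40% and 28%. They do not show that the trial is underpowered; they show that the protocol does not settle which power it has.

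**What to change.** In Basic power calculation, write: *244 per group, 488 in total; with 15% loss to outcome, 488/0.85 = 575, or 576 in equal groups, to have 80% power.* State that the test is two-sided and the allocation 1:1, if that is what was intended. This wording also replaces the phrase about obtaining significant differences. Then give the same figure in Participants. 576 is also a whole number of blocks of 6 (96 × 6).

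If the source cohort cannot be relied on to supply 576, keep 500-600 and restate the power as about 74% to 82% with 15% loss of outcome data, or 81% to 88% with complete follow-up at the assumed rates. Say which assumption applies, consistently with the Dropouts section.

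The cost of either route is protocol wording. The first raises the stated minimum by 15 or 16 people, and the second admits a lower power at the bottom of the range if outcomes are lost.
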